|                 | 
n=190; assuming a 10% screening failure rate approximately.
 
To be allocated to trial:
n=170 patients with active AS despite treatment with NSAIDs alone will be included in the phase I of the trial and treated with Golimumab. Only patients with good clinical response after 12 weeks of treatment will be enrolled in the phase II of the trial. It is assumed that approximately 60% (n=100) of patients included in phase I will continue in the phase II of the study, considering that elevated CRP at baseline is currently the best response predictor for TNF-blocker therapy.
 
To be analysed:
n=100 (n=50 in each group) patients will enter phase II of the trial (intention-to-treat population - ITT) after 1:1 randomization.
 
Statistical analysis:
 
Efficacy:
Efficacy of the therapy in reduction of radiographic spinal progression will be assessed by the modified Stoke Ankylosing Spondylitis Spine Score (mSASSS). mSASSS is a radiographic score measuring structural changes in the lumbar and cervical spine. Images will be scored by 2 trained readers in a blinded manner that allows the open-label (although randomized) design of the trial.
The primary efficacy endpoint will be radiographic spinal progression assessed by the change in the mSASSS score over two years of therapy in both groups. The primary analysis will be based on the intention-to-treat population, a secondary one in patients with complete sets of radiographs at two time points. A two-sided Mann-Whitney U-test will be applied to compare the mSASSS progression between both treatment groups in both analyses.
 
Safety:
Safety outcome will include absolute number and percentage of patients who experienced adverse events (AE), serious AE, AE of interest (infections, malignancies, gastrointestinal events: ulceration, bleeding, perforation, gastric outlet obstruction; thrombotic cardiovascular events: myocardial infarction, stroke, pulmonary artery embolism, peripheral arterial of venous thrombosis; renal and hepatic function deterioration), as well as a proportion of patients who discontinued the study because of AEs.
In order to address possible long-term safety issues related to long term use of NSAIDs a safety Follow-Up Visit will be performed 3 months after discontinuation of the study treatment (either week 108 or the last study visit in the case of early discontinuation).
Safety population will include each patient who received at least one dose of Golimumab with or without Celecoxib. Statistical comparisons will be based on event rates per 100 patient years of exposure. Rates will be compared by exact Poisson methods.
 
Secondary endpoint(s):
Mann-Whitney U-test, linear mixed models, and Chi-square test will be used in order to evaluate differences in the secondary outcome parameters between treatment groups.
 |

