## 7 SAFETY CONSIDERATIONS

### 7.1 Definition and Reporting of Adverse Events

An adverse event (AE) is defined as any new undesirable medical occurrence in a clinical investigation subject / patient having received at least one dose of a study drug; this does not necessarily have to be a causal relationship with the study treatment. An AE can therefore be any unfavourable and unintended sign (including an abnormal laboratory finding, for example), symptom, or disease during the time course of the study.

Such an event can result from use of the drug as stipulated in the trial or labelling, as well as from accidental or intentional overdose, drug abuse, or drug withdrawal. Any worsening of a pre-existing condition or illness is considered an AE. Worsening in severity of a reported AE should be registered as a new AE. Laboratory abnormalities and changes in vital signs are considered to be AE only if they result in discontinuation from the study, needs therapeutic medical intervention and/or if the investigator considers them to be an AE.

Following the subject's written consent to participate in the study, all serious AEs (SAE) should be collected. All other AEs should be collected throughout the treatment period from Week 0 until Week 108 and 4 weeks thereafter in the "Safety-Follow-up Visit" at Week 112.

If AEs occur, the subject should be followed until resolution or stabilization, and reported as serious AEs if the AE becomes serious. This also applies to subjects experiencing AEs that cause interruption or discontinuation of the investigational product, or those experiencing AEs that are present at the end of their participation in the study; such subjects should receive post-treatment follow-up as appropriate. If an on-going AE changes in its severity or in its perceived relationship to study drug, a new AE entry for the event should be completed.

A pre-planned elective surgery/procedure scheduled to occur during the study will not be considered an AE if the surgery/procedure is being performed for a pre-existing condition and no worsening of the pre-existing condition occurred during the study.

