#### 13.1 Definition of Population for Analysis

Primary analysis will be based on the ITT population. A secondary analysis will be based on all patients with complete sets of radiographs. For the purpose of safety analyses all patients receiving at least one dose of study drug (starting at Visit 2) will be included.

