#### 13.4 Safety Population

The safety population is defined to include all subjects who received at least one dose of the trial medication, whether withdrawn prematurely or not.

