### 13.5 Efficacy analyses

The primary analysis will be based on all patients who entered phase II of the trial (ITT population). Multiple imputation methods with mSASSS score at baseline as covariate (SAS procedure PROC MI) will be applied to deal with missing radiographs in the primary analysis. The Mann-Whitney test will be used to compare the primary outcome (change in the mSASSS score) between the treatment groups. Cumulative probability plots of will be built to visualise the finding.

In a secondary analysis the Mann-Whitney test will be used to compare radiographic progression in the subgroup of patients with complete sets of radiographs. A likelihood approach will be applied to deal with missing data in secondary outcome parameters assessed at multiple time points (Molenberghs G., Kenward M.G. Missing data in clinical studies. Chichester: John Wiley & Sons; 2007). For that reason linear mixed models (SAS procedure PROC MIXED) will be applied to compare means of secondary outcome parameters over time. Time and group, (time\*group) will be included in these models as fixed effects and patient-ID as a random parameter (included in PROC MIXED via the repeated statement with type = un for an unstructured covariance matrix). In the case of skewed data PROC MIXED will be applied to log-transformed parameter (CRP) or non-parametric tests (Mann-Whitney test, non-parametric analysis of covariance) will be applied (e.g., for biomarker data). Spearman rank correlation and non-parametric analysis of covariance will furthermore be used to investigate the association between radiographic progression and biomarkers of inflammation and bone/cartilage turnover (Bathke A, Brunner E. A nonparametric alternative to analysis of covariance. In: Akritas MG, Politis DN eds. Recent advantages and trends in nonparametric statistics. Amsterdam: Elsevier Science and Technology 2003: 109-20).

Nonresponder imputation for missing response data and chi-square tests will additionally be applied to compare response rates. Two-sided p values < 0.05 will be considered to be statistically significant.

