### 13.8 Sample Size and Power Calculation

The study is designed for a total sample size of  $n = 170$  subjects who will enrol in the phase I of the study. The power calculations are based on the findings of Kroon et al, our own results from GESPIC Cohort, and those of Braun et al. We assume a worsening in the mSASSS score of  $1.7 \pm 2.8$  in patients of the control group and of  $0.2 \pm 1.6$  in patients with continuous NSAIDs intake. We considered such a difference of 1.5 mSASSS units as clinically relevant and planned the sample size of this study by means of a two-sided ( $\alpha = 0.05$ ) Welch-Satterthwaite t-test accordingly. A smaller treatment effect, which was

observed in a trial comparing diclofenac continuously vs. on demand and which would be missed by our trial design, would be considered as clinically not relevant. To detect the difference with an 80% power, the sample size of  $n = 38$  in each group is needed in the phase II of the trial. This is also true if the Mann-Whitney test is applied. Since in the case of skewed non-normal distributions (like the mSASSS) the power of the Mann-Whitney-test is not lower than that of the t-test even in the case of ties (Rasch D et al, 2007). However, the power will decrease by the application of multiple imputations to deal with missing radiographs of dropouts in the ITT population. We estimated this decrease by: a) an estimation of dropout rates and b) the use of own mSASSS data. Considering that all subjects enrolled in the phase II will be responders to Golimumab therapy receiving this same treatment for the whole period of the trial, along with our experience in conducting randomized controlled trials, we presume dropout rates of less than 20% during phase II. For this reason and based on our own mSASSS data, we expect an increase in the variance of mSASSS progression because of multiple imputation by less than 25%. Considering this possible increase, a sample size of  $n = 100$  patients is needed for phase II of the trial to detect the expected and clinically relevant difference of an average 1.5 mSASSS points with an 80% power in the ITT population. In addition we assumed that 60% of the subjects enrolled in phase I of the study ( $n = 100$  out of 170) would be eligible for randomization and participation in phase II (based on the rate of the BASDAI response of at least 2 absolute points in AS patients with elevated CRP).

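### The only safety set for the between-arm rate comparison starts at week 0 and is not limited to randomised time, and the exact Poisson test is too liberal for common recurrent adverse events

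*Protocol*

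**What the plan says.** The protocol defines the safety population in three places, and all three start at the first golimumab dose.

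- Synopsis, safety analysis: "Safety population will include each patient who received at least one dose of Golimumab with or without Celecoxib".
- Section 13.1: for safety, "all patients receiving at least one dose of study drug (starting at Visit 2) will be included". Visit 2 is week 0, twelve weeks before randomisation.
- Section 13.4: "The safety population is defined to include all subjects who received at least one dose of the trial medication, whether withdrawn prematurely or not".

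Directly after its definition the synopsis sets the comparison: "Statistical comparisons will be based on event rates per 100 patient years of exposure", and "Rates will be compared by exact Poisson methods". It gives no time window, no rule for assigning run-in time to an arm, and does not say whether all events or first events are counted. Section 13.6 is descriptive and does not mention the rate comparison.

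For efficacy the protocol does draw the line at randomisation. Section 13.2 starts the intention-to-treat set at Visit 6, and section 13.7 says that only patients eligible for randomisation are the target population.

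Section 5.2 lists both the number of adverse events and the percentage of patients with events. On recording, section 7.1 says: "Worsening in severity of a reported AE should be registered as a new AE". It also requires a new entry when the perceived relationship to study drug changes.

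**The concern.** Randomisation protects only the comparison of the two arms from week 12 onwards. A safety set that opens at week 0 brings in person-time that nobody was randomised to, and patients who never had an arm. Under section 6.2.2 patients keep their own NSAID at a stable dose during the run-in, whereas section 6.2.1 encourages the control arm to stop NSAIDs at week 12. Run-in time is therefore not comparable with either arm, on a question that is itself about NSAID safety.

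The test is a second matter. An exact Poisson comparison treats events as independent, with variance equal to the mean. When one patient can contribute many events, and one illness several entries, total counts vary more than that and p-values come out too small.

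Section 4.3.3 says that any benefit on spinal progression must be weighed against the risks of continuous NSAID use. The safety comparison supplies one side of that balance.

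**Working it through.** The protocol gives no rate, exposure or power figure for safety, so there is no stated figure to reproduce.

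**Inputs from the protocol.** 170 patients enter the run-in and 100 are randomised 1:1 (synopsis, section 13.8), so about 70 are never randomised. The run-in lasts 12 weeks and phase II lasts 96. The two-sided 5% level is stated in section 13.5 for efficacy ("Two-sided p values < 0.05 will be considered to be statistically significant") and is assumed here for safety.

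**Assumptions, not in the protocol.** *k* is the run-in event rate divided by the phase II control rate, from 0.5 to 3. Events per patient in phase II run from 0.18 to 6. Between-patient variation is gamma-distributed.

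**Step 1: exposure** (52 weeks per year, full follow-up)

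- Whole run-in: 170 × 12/52 = 39.2 patient-years
- Never-randomised patients: 70 × 12/52 = 16.2
- Own run-in of each arm: 50 × 12/52 = 11.5
- Phase II per arm: 50 × 96/52 = 92.3

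With 20% drop-out at mid-period on average, phase II falls to 92.3 × (1 − 0.2 × 0.5) = 83.1 per arm, and the run-in weighs more.

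**Step 2: observed rate ratio under three attributions**, for true ratio R

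- A, all run-in time counted as golimumab alone: R ÷ [(92.3 + 39.2k)/131.5]
- B, run-in kept with the later arm, never-randomised patients left out: (92.3R + 11.5k)/(92.3 + 11.5k)
- C, as B, with never-randomised patients added to golimumab alone: [(92.3R + 11.5k)/103.8] ÷ [(92.3 + 27.7k)/120.0]

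| k | A, R = 1 | B, R = 1 | C, R = 1 | A, R = 2 | B, R = 2 | C, R = 2 |
|---|---|---|---|---|---|---|
| 0.5 | 1.18 | 1.00 | 1.07 | 2.35 | 1.94 | 2.07 |
| 1 | 1.00 | 1.00 | 1.00 | 2.00 | 1.89 | 1.89 |
| 1.5 | 0.87 | 1.00 | 0.95 | 1.74 | 1.84 | 1.74 |
| 2 | 0.77 | 1.00 | 0.90 | 1.54 | 1.80 | 1.63 |
| 3 | 0.63 | 1.00 | 0.84 | 1.25 | 1.73 | 1.44 |

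Under A, a true ratio of 1.3 reads 1.3/1.149 = 1.13 at k = 1.5 and 1.3/1.298 = 1.00 at k = 2. B leaves a null effect at 1.00 for every k and only dilutes a real one.

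**Step 3: type I error of the exact Poisson test**, 50 per arm, phase II only

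With mean m events per patient and gamma shape s, the variance is m(1 + m/s). The approximate error is 2[1 − Φ(1.96/√(1 + m/s))]. The simulated column is the exact conditional test, 20,000 runs.

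| m | s | 1 + m/s | Approximate | Simulated |
|---|---|---|---|---|
| 1 | 2 | 1.5 | 11% | 9% |
| 4 | 2 | 3 | 26% | 25% |
| 6 | 2 | 4 | 33% | 31% |
| 4 | 1 | 5 | 38% | 37% |
| 6 | 1 | 7 | 46% | 45% |

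With no extra variation the simulated error is 2.8% to 4.7%. For rare events (0.1 per patient-year, about 0.18 per patient) it is 3.6% to 6.3%, even with shape as low as 0.5. A test that uses the observed between-patient variance (Welch t-test on per-patient counts) stays between 4.4% and 5.2% throughout.

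**The case against.** The best defence is that an all-treated safety set is conventional and that the protocol fixes only the population. It does not say which person-time enters each arm's rate, and a statistical analysis plan that is not shown could settle that. Treatment groups exist only from week 12, so the natural reading keeps each patient with the randomised arm and leaves never-randomised patients out of the comparison. That is attribution B, which dilutes and does not confound.

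Much of this stands. A reader might infer that the protocol counts all run-in time as golimumab alone, so that the arms are confounded and a celecoxib risk is hidden. The protocol does not say so. The direction of bias under that reading depends on *k*: below 1 the celecoxib risk is exaggerated, above 1 it is masked. Nor is the run-in clearly free of celecoxib, since patients continue their own NSAID and the ban on celecoxib is written for the control group.

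A reader might also infer that the Poisson p-values are too small in general. That fails for the rare events of interest and for first-event counts. The protocol does not specifically prescribe a test of total counts, and section 13.6 treats overall adverse events descriptively. Section 7.1 is a recording rule and is not in itself an error.

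The defence does not dispose of the point. The synopsis places its rate comparison immediately after a week-0 population, no other safety set is defined, and attribution B has to leave out patients whom the stated population includes. The test is named without any limit to rare or first events, while the number of adverse events is an endpoint.

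**Conclusion.** The point holds in a bounded form. The protocol ties its between-arm rate comparison to a safety set with about 39 patient-years of unrandomised exposure, about 16 of them from patients never randomised, and does not restrict it to randomised phase II time. At best this dilutes a real difference (2.0 to between 1.94 and 1.73). If run-in or never-randomised time is counted as golimumab alone, a null ratio of 1.0 can read anywhere from 1.18 to 0.63. Those ranges rest on an assumed *k* of 0.5 to 3.

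Exact Poisson testing is anti-conservative for total counts of common recurrent events, with error of about 9% to 37% over most of the assumed range and about 45% at six events per patient with shape 1. It is adequate for rare events. Event rates and dispersion are assumptions; the protocol gives neither.

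This should be corrected, but it does not show that the arms will be confounded or that every safety p-value is unreliable.

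**What to change.** - Define a phase II safety set by arm: patients dosed from Visit 6, with events by onset and person-time from the week-12 dose. Use it for every between-arm safety comparison.
- Keep the all-treated set from week 0, and describe the run-in and the never-randomised patients separately, without an arm comparison.
- Compare total adverse event counts with a negative binomial or robust-variance model with a log-exposure offset. Count entries that record only a change in severity or perceived relationship as one event.
- Keep exact Poisson methods for rare events of interest or first occurrences, and say which of these is counted.
- Align the synopsis with sections 13.1, 13.4 and 13.6.

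The cost is wording in the protocol and analysis plan, plus modest programming. No new data or visits are needed, because event dates and dosing dates are already recorded.

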
3 ASSESSMENT SCHEDULE

| Study phase                               | Phase I                              |                      |                         |                         |                         |                          | Phase II                  |                           |                           |                           |                           |                           |                           |                                            |                                             |
|-------------------------------------------|--------------------------------------|----------------------|-------------------------|-------------------------|-------------------------|--------------------------|---------------------------|---------------------------|---------------------------|---------------------------|---------------------------|---------------------------|---------------------------|--------------------------------------------|---------------------------------------------|
|                                           | Screening
≤ 6 weeks
(-42 days) | Baseline
(week 0) | Week
2*
(±7 days) | Week
4*
(±7 days) | Week
8*
(±7 days) | Week
12*
(±7 days) | Week
24*
(±14 days) | Week
36*
(±14 days) | Week
48*
(±14 days) | Week
60*
(±14 days) | Week
72*
(±14 days) | Week
84*
(±14 days) | Week
96*
(±14 days) | Week
108*/ET a
(±14 days) | Week
112 / FU b
(±14 days) |
| Study Procedures                          | Visit 1                              | Visit 2              | Visit 3                 | Visit 4                 | Visit 5                 | Visit 6                  | Visit 7                   | Visit 8                   | Visit 9                   | Visit 10                  | Visit 11                  | Visit 12                  | Visit 13                  | Visit 14                                   | Visit 15                                    |
| Informed consent                          | X                                    |                      |                         |                         |                         |                          |                           |                           |                           |                           |                           |                           |                           |                                            |                                             |
| Inclusion/Exclusion criteria              | X                                    | X c       |                         |                         |                         | X                        |                           |                           |                           |                           |                           |                           |                           |                                            |                                             |
| Randomization                             |                                      |                      |                         |                         |                         | X                        |                           |                           |                           |                           |                           |                           |                           |                                            |                                             |
| Demographics                              | X                                    |                      |                         |                         |                         |                          |                           |                           |                           |                           |                           |                           |                           |                                            |                                             |
| Medical/Surgical history                  | X                                    | X c       |                         |                         |                         |                          |                           |                           |                           |                           |                           |                           |                           |                                            |                                             |
| Vaccination status                        | X                                    |                      |                         |                         |                         |                          |                           |                           |                           |                           |                           |                           |                           |                                            |                                             |
| Prior/concomitant medication              | X                                    | X                    | X                       | X                       | X                       | X                        | X                         | X                         | X                         | X                         | X                         | X                         | X                         | X                                          |                                             |
| Adverse events                            |                                      | X                    | X                       | X                       | X                       | X                        | X                         | X                         | X                         | X                         | X                         | X                         | X                         | X                                          | X                                           |
| Vital signs d                  | X                                    | X                    | X                       | X                       | X                       | X                        | X                         | X                         | X                         | X                         | X                         | X                         | X                         | X                                          |                                             |
| Weight and height                         |                                      | X                    |                         |                         |                         | X                        |                           |                           |                           | X                         |                           |                           |                           | X                                          |                                             |
| Smoking assessment e           |                                      | X                    |                         |                         |                         | X                        |                           |                           |                           | X                         |                           |                           |                           | X                                          |                                             |
| Physical examination                      | X                                    | X                    | X                       | X                       | X                       | X                        | X                         | X                         | X                         | X                         | X                         | X                         | X                         | X                                          |                                             |
| Major AS assessment f          |                                      | X                    |                         |                         |                         | X                        |                           | X                         |                           | X                         |                           | X                         |                           | X                                          |                                             |
| Minor AS assessment g          | X                                    |                      | X                       | X                       | X                       |                          | X                         |                           | X                         |                           | X                         |                           | X                         |                                            |                                             |
| ECG h                          | X                                    |                      |                         |                         |                         |                          |                           |                           |                           |                           |                           |                           |                           |                                            |                                             |
| Blood analysis i               | X j                       | X                    | X                       | X                       | X                       | X                        | X                         | X                         | X                         | X                         | X                         | X                         | X                         | X                                          |                                             |
| Biomarker blood samples k      |                                      | X                    |                         |                         |                         | X                        |                           |                           |                           | X                         |                           |                           |                           | X                                          |                                             |
| Urinalysis                                | X                                    | X                    |                         | X                       |                         | X                        |                           | X                         |                           | X                         |                           | X                         |                           | X                                          |                                             |
| Serum pregnancy test l         | X                                    |                      |                         |                         |                         |                          |                           |                           |                           |                           |                           |                           |                           |                                            |                                             |
| Stool samples m                |                                      | X                    |                         |                         |                         | X                        |                           |                           |                           |                           |                           |                           |                           | X                                          |                                             |
| Hepatitis B screening (HBs-Ag, anti-HBc)  | X                                    |                      |                         |                         |                         |                          |                           |                           |                           |                           |                           |                           |                           |                                            |                                             |
| Tuberculosis IGRA test n       | X n                       |                      |                         |                         |                         |                          |                           |                           |                           |                           |                           |                           |                           |                                            |                                             |
| Chest X-ray n                  | X n                       |                      |                         |                         |                         |                          |                           |                           |                           |                           |                           |                           |                           |                                            |                                             |
| X-ray of the spine o           | X o                       |                      |                         |                         |                         |                          |                           |                           |                           |                           |                           |                           |                           | X o                             |                                             |
| MRI of spine and SIJ p         | X p                       |                      |                         |                         |                         |                          |                           |                           |                           |                           |                           |                           |                           | X p                             |                                             |
| Study drug – administration at study site |                                      | X                    |                         | X                       | X                       | (X)                      |                           |                           |                           |                           |                           |                           |                           |                                            |                                             |
| Study drug issuance                       |                                      |                      |                         |                         |                         | X                        | X                         | X                         | X                         | X                         | X                         | X                         | X                         |                                            |                                             |
| Returned drug account                     |                                      |                      |                         |                         |                         |                          | X                         | X                         | X                         | X                         | X                         | X                         | X                         | X                                          |                                             |

\*Weeks after first Golimumab administration, study visits 3 to 6 have a time window of  $\pm 7$  days, and the study visits 7 to 15 – a time window of  $\pm 14$  days. If a subject has an out of window visit the next visit should occur according to the original schedule based on the date of the baseline visit (Visit 2 / Week 0)

a. ET = early termination visit only for subjects who prematurely discontinue study in the Phase II for any reason; should be performed within 4 weeks of last dose of study drug.

b. FU = Follow-up phone visit, collection of the safety information; to be performed 12 weeks after Week 108/ET visit.

c. Interim history.

d. Heart rate, blood pressure.

e. Former and actual smoking state at baseline, actual smoking status at subsequent visits.

f. Spinal mobility (BASMI), function (BASFI), disease activity (BASDAI, ASDAS, overall pain, night pain, PASS, PhASS), global assessment (patient/physician), overall health status / quality of life (ASAS health index).

g. BASDAI, ASDAS, PASS, PhASS, patient and physician global assessment only.

h. 12-lead electrocardiography (ECG).

i. Lab tests to be performed locally at the clinical trial site: Blood chemistry (total bilirubin, ALT, AST, GGT, AP, creatinine), hematology (erythrocytes, hemoglobin, leucocytes, neutrophils, lymphocytes, monocytes, basophils, eosinophils, platelets), CRP and ESR.

j. Lab test at screening should include also Quick-Test, International Normalized Ratio (INR) and activated Partial Thromboplastin Time (aPTT)

k. Biomarker blood samples (soluble and cellular markers of inflammation, cartilage and bone turnover) to be transferred to the Charité Universitätsmedizin Berlin.

l. Female patients of child-bearing potential only.

m. Stool samples for the microbiome analysis to be transferred to the Charité Universitätsmedizin Berlin.

n. Chest x-ray & tuberculosis serum IGRA test (QuantiFERON® TB Test or T SPOT.TB®) performed within 3 months prior to screening can be accepted.

o. X-rays of the lumbar and cervical spine, lateral views; to be performed at screening only if there is no image performed within 24 months prior to screening; at visit "Week 108/ET" – to be performed only at or after week 84 in case of early termination. All images of the spine to be transferred to the study coordinating centre at the Charité for central reading.p. For centres and patients participating in the MRI sub-study only. At visit "Week 108/ET" only to be performed at or after week 84 in case of early termination.

